#### **D.10.B Women enrolled in observational study ONLY (CT only)**

The one-time mailed questionnaire will contain questions on medical history, demographics, quality of life, physical activity, and diet.

#### **Women enrolled in exercise vs. health education study**

**Blood draw, Processing, and Storage:** Fasting blood (> 12 hours) will be drawn at baseline and six months in a standardized fashion. Two 10ml red-top tubes will be collected for serum, and a 10ml light blue-top and 10ml lavender-top will be collected for citrate and EDTA plasma. Technicians in the lab will centrifuge the samples at 2,000 rpm for 15 minutes at 4°C. Plasma and buffy coat will be separated and transferred into cryovials and labeled with freezer-proof labels with participant ID #s and date. Saliva samples will be collected by each participant for the 4 days prior each clinic visit (baseline and 6 months) and will be stored in the participant's fridge overnight in a sealed plastic bag. Saliva samples will be collected at wakeup and at bedtime. All specimens collected will be stored temporarily at 4°C during transportation or prior to delivery to the site's freezers, and then stored at -70°C until time of analysis. The specimens will be stored in an organized storage system with unique location identifiers based on freezer compartment number, rack number, box number, and slot number. The freezers are configured with beepers, dial-up alarm systems and CO2 backup systems in the event of a power failure or change in temperature.

#### **Hormones:**

Six cancer-related proteins—leptin, prolactin, osteopontin, IGF-II, macrophage inhibitory factor (MIF), and CA-125—will be measured at in the baseline and 6-month blood samples. Previous studies had identified each of the six proteins as possible biomarkers of ovarian cancer risk and prognosis. For the proposed study we will examine the effect of exercise on certain hormones associated with obesity and physical activity in studies of healthy women and women with breast cancer (insulin, IGFs, and sex hormones). We will also examine the effect of exercise on additional biomarkers shown to be associated with ovarian cancer risk and prognosis (i.e., CA-125, osteopontin, prolactin, and MIF).

Baseline and six-month hormones will be measured. Each woman's baseline and follow-up samples will be measured in the same batch, and an equal number of intervention and control samples will also be included in the same batch. Appropriate quality control samples (low and high levels) will be used to monitor the reliability of each assay. Each plate will measure 40 samples and include two sets of quality control (QC) samples. One set of the QC is internal QC that is provided in each kit. Any assay with its internal QC values out of the suggested range will be disregarded and the assay will be repeated. The second set of QC is external QC purchased from a different commercial source. The results of external QC will be analyzed after all measurements are completed. Plates with external QC values greater or less than 2 standard deviation of the mean QC will be repeated. Also, in each assay run, samples with greater than 20% of coefficient of variation in their duplicated results will be repeated. Blind duplicates are also included in and between batches to estimate coefficient of variations.

**Insulin:** Insulin will be measured via radioimmunoassay using guinea pig antibodies to porcine insulin. I-Insulin (porcine) will be used as the radioactive tracer. Samples and serial dilutions of insulin standards (human) will be incubated with antibody and tracer for 4 hours at room temperature. Antibody bound insulin will then be precipitated by a second antibody (goat anti guinea pig gamma globulin), 10% guinea pig serum, and polyethylene glycol and precipitated complex is counted in a gamma counter for measurement and data reduction. The intra- and inter-assay CVs are 6.5% and 9.3%.

**IGFs:** Plasma concentrations of total IGF-1, IGF-2 and IGFBP-3 will be determined with the use of immunoassays. In order to make our results comparable with the findings published in literature, we will use commercially available immunoassay kits from Diagnostic Systems Laboratories, Inc. (Webster, TX). The analytic methods for total IGFs are enzyme-linked immunosorbent assays (ELISA), which are designed to quantify concentrations of total IGF-1, IGF-2 and IGFBP-3 either in serum or in plasma. Since ELISA employs two specific antibodies to form a sandwich complex with their corresponding antigens, this type of method provides better sensitivity and specificity than other competitive immunoassays. The assays have little cross reactivity with other closely related antigens and the results are reproducible. The assays will be performed following the manufacturer's instructions.

**Leptin and CRP:** Leptin will be measured by direct RIA using kits from Linco (St. Charles, MO), whereas CRP will be measured with direct chemiluminescent immunoassay on the Immulite analyzer (Diagnostic Products Corporation (DPC, Los Angeles, CA). Intra-/Inter-assay CV percents for each assay range from 4.1 (leptin) to 10.8 (CRP).

**CA-125, Osteopontin, Prolactin, and MIF:** Given [name] has performed many assays of these hormones in order to develop his ovarian cancer screening test, he will analyze these specific hormones in his lab. He will use commercially available immunoassay kits from Diagnostic Systems Laboratories, Inc. (Webster, TX). The analytic methods are enzyme-linked immunosorbent assays (ELISA), which are designed to quantify concentrations of these hormones either in serum or in plasma. Since ELISA employs two specific antibodies to form a sandwich complex with their

corresponding antigens, this type of method provides better sensitivity and specificity than other competitive immunoassays. The assays have little cross reactivity with other closely related antigens and the results are reproducible. The assays will be performed following the manufacturer's instructions.

**Other Hormone Assays:** We also will store blood for future ancillary hormone analyses (e.g., androgens or markers of inflammation). Baseline study consents from participants will allow future ovarian cancer-related analyses with these samples.

**Salivary cortisol:** Women will be asked to collect 2 saliva samples (wake up and bedtime) for 4 days prior to the baseline clinic visit and the final clinic visit. Analysis of samples will be conducted at YCCI.

**Tumor specimens:** At baseline, we will request consent from the participants to obtain tumor specimens for future ancillary studies relating to ovarian disease, including investigating the role of tumor characteristics in the prognosis of ovarian disease.

**D.11. Medical Record Abstraction and Physician Verification of Treatment Reports:** The following will be obtained via a Physician Verification of Treatment Report or abstraction from the medical records: clinical stage, therapy received (chemotherapy/surgery/radiation) and treatment dates.

**D.12.A Exercise Intervention:** Given the primary side effect of ovarian cancer surgery and treatment is fatigue, and given exercise has had a favorable impact on fatigue in breast cancer survivors, we hypothesize that a similar intervention adapted for ovarian cancer survivors will increase physical activity levels, and this increase in activity will have a favorable impact on fatigue, QOL and surrogate markers of survival. However, given that another symptom reported by ovarian cancer patients may include peripheral neuropathy, we will individualize and modify the exercise program based on any special needs secondary to surgery and treatment (e.g., if the participant is experiencing peripheral neuropathy, then we will recommend supervised exercise at the gym or recommend other activities such as swimming, stationary recumbent bicycling and/or upper body ergometry). The exercise program will also be individualized based on the participant's history of participation in physical activity and her preferred type of exercise.

The exercise intervention will consist primarily of a home-based moderate-intensity aerobic exercise program, e.g., brisk walking. However, our intervention also includes other exercise settings/approaches (e.g., access to health-club, monthly in-person "booster" sessions, monthly physical activity events and newsletters) in an effort to maximize the number of participants who meet and maintain the study's physical activity goals. Because our trial is focusing on efficacy and ensuring a high adherence rate, then it is paramount that we offer a number of different components to increase physical activity participation. If we show a favorable effect of exercise on QOL and prognosis, then future trials may examine effectiveness of exercise and whether one method of increasing physical activity is superior to another.

#### **Exercise Settings/Approaches**

**Immediately post-randomization:** Women randomized to the exercise group will be taught exercise techniques and principles in an initial in-person visit either at their home, at a local gym (we have budgeted for the purchase of a six-month membership for all women randomized to exercise so that participants have daily access to a local gym), or via phone. At this visit or phone call, each participant will get to know the exercise trainer, who has the primary responsibility for delivering the intervention (including telephone delivery), eliciting motivation from the participant to achieve goals, and assuring completion of required data collection. The exercise trainer will be a part of the study's personnel, and not a gym employee. While the local gym's exercise trainers will be aware of the trial, we will not be asking them to help with data collection or to carry out the intervention.

**Telephone Delivery:** Participants will also be taught exercise techniques and behavior change strategies via the telephone (weekly phone calls for months 1-6). The telephone counseling protocol is the principal instrument used to promote exercise adherence in the exercise group. Telephone contact has proven to be effective (and cost effective) for the adoption and maintenance of physical activity in

healthy and cancer populations (65). The study's counseling protocol, based on our previous research (the IMPACT study, Section C.2) and the Cooper Institute's *Active Living Every Day* workbook (based on Project Active) (66), follows a stepwise, phased approach using strategies outlined by social cognitive theory and theory of planned behavior (see section below), indicating that the optimal intervention for a major behavior change should focus on 1) helping the person establish a sequential series of short-term goals and b) enabling the person to review and judge performance on these goals in a way that builds self-efficacy. Our intervention will follow a three-phase protocol: Phase 1 (months 1 and 2) involves education and rapid development of self-efficacy to help participants realize they can change their physical activity; Phase 2 (months 3 and 4) involves self-monitoring and overcoming barriers; and Phase 3 (months 5 and 6) involves motivational reminders and preventing noncompliance. As well as discussions about exercise, the exercise trainer will discuss a health topic of interest each week, information that is given to those in the Health Education group. Inclusion of this information will make the groups comparable with the exception of the exercise intervention.

At the beginning of the study, the participant and exercise trainer will agree upon a regular time to talk on the telephone (see Quality Assurance of Intervention for training of telephone delivery). During each phone call the exercise trainer will discuss the participant's past week physical activity level, any barriers to exercising, and will educate her on how to maintain her exercise program. For the proposed study, the educational material and telephone scripts have already been pilot tested in the IMPACT Study. The participant will record her daily sports/recreational activity in the Daily Activity Log. Every four weeks (after completing the pedometer log), participants will return, via stamped, addressed envelopes, the Daily Activity Log. During the weekly motivational phone calls, the exercise trainer will remind the participant to return her completed Logs to the study office. The physical activity logs will be reviewed by the exercise trainer.

If the participant is not available during the regularly scheduled time to talk, the exercise trainer will make two more phone call attempts later that day or the next day, followed by an email notification (if the participant has access to email). The exercise trainer will document any missed calls and number of attempts to contact the participant. If the exercise trainer is still unable to contact the participant within one week of the scheduled time, then a letter will be mailed to the participant encouraging her to contact the exercise trainer or study staff. Weekly staff meetings between the PI, project manager and exercise trainer will occur, and further discussion as to how to reach the participant will be discussed. Once the exercise trainer contacts the participant, a further discussion of the study goals occurs. Participants are told that meetings, as well as complete, accurate, and timely reports of their physical activity, are critical to the trial's success. Although the study is designed to be primarily a telephone counseling intervention, the exercise trainer will allow flexibility, such that for example, for women who are too busy in a particular week to have a phone call, interaction can be done via email or instant messaging.

**Health-Club Delivery:** In addition to the telephone counseling, participants will be provided with a six-month gym membership, which will allow them to exercise at a gym especially during inclement weather and in the evenings. The successful Diabetes Prevention Program offered gym access to their lifestyle participants, as does Look AHEAD for participants not adhering to the exercise prescription. The exercise trainer will visit with participants at least monthly either in the gym, the participant's home or neighborhood. Each meeting will feature a theme that promotes adherence and offers novelty while reinforcing the exercise goals prescribed earlier (e.g., "Ways to stay motivated"), in addition to further educating participants on how to exercise safely and at the appropriate intensity.

**Voluntary Monthly Events:** We also will have voluntary monthly events in CT (e.g., hikes, walks, involvement in local road races) to further motivate the participants to adhere to the exercise program. These events will also provide additional social support and allow the participants to reach particular goals or milestones (e.g., participating in a 5k road race).

**Newsletters:** The quarterly newsletters will feature research updates, physical activity information focused on helping to motivate the participants to maintain the exercise prescription, participant spotlights, and ovarian cancer and general health related information.

**Cohort Maintenance Program:** Participants will receive other mailings (e.g., birthday cards). In addition, there is the option of “refresher” meetings at the health club or additional individual telephone contact for participants having a difficult time adhering to the exercise prescription.

**Exercise Prescription:** The exercise intervention will consist primarily of walking with an eventual goal of 150 min/week of moderate-intensity aerobic activity. Our recommended amount of exercise is based on current physical activity guidelines of 30 min/session of moderate-to-vigorous intensity aerobic exercise on most days of the week (84). While we will advise our participants to reach this weekly exercise goal with daily exercise sessions, some women may prefer to achieve this through longer sessions on fewer days. However, we will discourage excessive durations at one session to avoid injuries. All exercise sessions will begin with 5 min stretching warm-up, and will end with 5 min cool down. Exercise will start at 50% of predicted maximal heart rate ( $220 - \text{age}$ ) and will be gradually increased in accordance with American College of Sports Medicine guidelines to approximately 60-80% of predicted maximal heart rate (69), with careful tailoring so that older, less fit women will be kept at the lower HR range. Heart rate will be electronically monitored with high/low pulse rate alarms individually set for each subject. Following each exercise session, participants will complete their Daily Activity Log, recording the type of exercise, duration, and average heart rate. The logs will be discussed during the telephone calls, and mailed in monthly to the Study office. If 150 min/week of aerobic exercise was not performed in the previous week, the exercise trainer and participant will discuss barriers experienced by the participant. Participants may participate in strength training, but it will not be counted towards the 150 min/wk goal.

**Theory of Planned Behavior:** Ajzen’s theory of planned behavior is a validated theoretical model that has been used to study exercise behaviors in cancer survivors (85). This theory proposes that intention is the immediate determinant of behavior because it reflects the person’s level of motivation and desire to exert effort. In turn, intention is thought to be determined by three independent constructs: attitude, subjective norm, and perceived behavioral control. Perceived behavioral control is defined as the perceived ease or difficulty of performing the behavior, and it may directly predict behavior if it is an accurate reflection of actual control. Attitude is viewed as a positive or negative evaluation of performing the behavior (e.g., good or bad), and subjective norm captures the perceived social pressure that individuals may feel to perform or not perform the behavior. The theory of planned behavior therefore proposes that (a) people will perform a behavior when they intend to do so and have the necessary control over it, and (b) people will intend to perform a behavior when they evaluate it positively, believe that important others think they should perform it, and perceive it to be under their own control. Prior to randomization, participants will complete the Theory of Planned Behavior questionnaire. We will tailor the intervention/telephone counseling based on their responses to the questionnaire and their level of intention. Participants assigned to the exercise group who have weaker intentions will be flagged and given more attention in terms of support and resources for behavior change. This will include highlighting possible incentives for exercise, proactively addressing any anticipated barriers to exercise, and securing social support from family members.

**Procedures to Enhance Adherence:** 1) Self-monitoring including use of physical activity logs, pedometers, and heart rate monitors delineating intensity, duration, and frequency; 2) Personalized (and written) feedback regarding baseline data with determination of individualized exercise program established from the baseline information; 3) Realistic (individualized) goals that can be updated on a regular basis; 4) Initial use of individual in-person instruction to teach concepts and techniques; 5) Weekly telephone counseling to facilitate overcoming barriers, give positive reinforcement, answer questions and inquire about and assess problems related to exercise; 6) Directly observing participants

exercise during the monthly health club meetings and physical activity events; 7) Group participant support and communication during the monthly meetings/events; 8) Quarterly physical activity summaries of the participant's adherence; and 9) Quarterly newsletters discussing ovarian cancer health and other health topics. Based on our past experience, and the strategies we will use, we expect a high adherence rate among the exercisers (~80%).

#### **Quality Assurance of Intervention**

**Training and Certification:** [name] will train the exercise trainer(s) in techniques of telephone counseling and behavior change. [name] has experience in conducting exercise trials in healthy women and cancer survivors that resulted in high adherence and compliance to the interventions. The exercise trainers will be required to attend two-day training sessions, conducted by [name], to review implementation of the physical activity protocol and to learn behavior change techniques. Exercise trainers will practice extensive role-playing before conducting their first counseling session. In addition to attending the training sessions, exercise trainers will be instructed to be conversant with the study's protocol and all intervention manuals. [name] and/or the project manager will supervise and review at least two individual participant training sessions by each trainer. Exercise trainers will also receive support and training through regular staff meetings, facilitated by the PI and the project manager, to discuss adherence of each participant and to resolve challenging issues.

**Summary and Benefits of our Exercise Intervention:** Our exercise intervention combines multiple exercise approaches in an effort to maximize the number of participants who meet the study's physical activity goals. The mix of individual and group counseling was selected to reap the potential benefits of each approach. A major strength of the health-club delivery approach is that participants will be able to exercise at times that are convenient to them and in all types of weather. The exercise trainers will also visit the health club at least monthly, allowing them to directly observe the participant exercising. These visits will especially be utilized to assist women who are having difficulty in meeting weekly exercise goals. Individual contact is critical to retaining participants; thus a major strength of using the telephone as the principal instrument of the intervention delivery is personalized and individualized attention and feedback on a regular basis.

**D.13.A Attention Control (Health Education) Group:** Given one of the primary outcomes is QOL, it is important that the exercise and health education groups are comparable in regards to the amount of attention provided. While, we have designed a control group to be matched on attention and time, it is important that there is no overlap in regards to information on exercise. Furthermore, it is important that the health education group is credible and/or of interest to women diagnosed with ovarian cancer.

We will telephone women randomized to the control group weekly to discuss health issues of interest to these patients. Thus, both exercise and control groups will be matched in regards to attention and time (i.e., weekly phone calls and monthly group meetings), but the content of the interventions will differ (i.e., exercisers will receive all the information the control group receives in addition to exercise training). Furthermore, each group will receive quarterly newsletters, but the content of the newsletters will differ for the exercise and control group. Lastly, incentives (\$50 Gift certificate) will be given to participants who comply with the study (i.e., return for 6-month clinic visits), but since these incentives are given at completion of the study, overlap should not be a concern.

Specifically, immediately after randomization, participants in the Health Education Group will be provided written information that emphasizes the importance of a healthy lifestyle. Participants will be encouraged to follow the NCI and ACS physical activity guidelines. This procedure was utilized in our other exercise trials, with no increase in physical activity levels observed at follow-up among women in the health education group. Health Education participants will also receive an equal number of contacts throughout the 6-month intervention as women randomized to exercise. Each week, women randomized to the health education group will receive phone calls to discuss a range of relevant health issues. We will develop handouts that will be discussed at the voluntary monthly meetings. At the end

of the intervention, the exercise trainer will call participants in the health education group to develop a personalized exercise program, which will be mailed to them.

At the end of the study participants in both groups will receive some individual results from the study from the baseline and 6-month visit (BMI, bone mass, body fat, weight, steps per day) and will be given information on survivorship resources in Connecticut.

**D.14. Data Processing, Storage, and Confidentiality:** We will use a Web-based clinical study data management system that is located on a secure server at Yale University to store and manage study data. Only [name] and her staff will have access to the database. Access will be by password protected.

**D.15. Study Timeline:** Data collection will take 4.5-5 years and will occur from month 6 through month 60. The total study is 5 years; thus allowing for 6 months lead setup time. The timeline we have proposed is similar to timelines followed in our other exercise trials. The first six months will be devoted to preparing questionnaires (note we already have working versions from our previous and ongoing trials), obtaining CT hospital IRB approvals, preparing for recruitment, establishing measurement procedures, planning the exercise intervention, and starting subject identification. Randomization of individuals will start at the beginning of month 6, and will continue until the end of month 48. Data entry and cleaning will be ongoing. Statistical analyses and report writing will begin around month 20 (manuscripts pertaining to study objectives and recruitment). We plan to present preliminary results at conferences in Year 2 - 5 of the study.

**D.16. Future Follow Up/Ancillary Studies:** We plan to obtain subject consent to recontact them for future studies.

**D.16.A Evaluation of Vital Status:** The National Death Index will be used to determine vital status of the participants 1-7 years following the completion of the study.

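### The Protocol states that the arms are matched on attention and number of contacts, but it schedules individual trainer contact for exercisers only, so a QOL difference would show the effect of the whole programme, not of exercise separately from that contact

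*Protocol*

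**What the plan says.** D.13.A sets its own standard. Because QOL is a primary outcome, "it is important that the exercise and health education groups are comparable in regards to the amount of attention provided". It then says the standard is met: "Thus, both exercise and control groups will be matched in regards to attention and time", explained as weekly calls and monthly group meetings. It adds that "Health Education participants will also receive an equal number of contacts throughout the 6-month intervention as women randomized to exercise". On content it is open that the arms differ: "exercisers will receive all the information the control group receives in addition to exercise training". The Telephone Delivery text in D.12.A gives the reason for sharing the weekly health topic with exercisers: "Inclusion of this information will make the groups comparable with the exception of the exercise intervention".

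The rest of D.12.A describes what exercisers receive beyond the calls:

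- an initial teaching session at home, at a gym or by telephone;
- individual trainer contact: "The exercise trainer will visit with participants at least monthly either in the gym, the participant's home or neighborhood";
- voluntary monthly events in Connecticut, a six-month gym membership and newsletters;
- optional refresher meetings or further individual calls for women who struggle with the prescription;
- under Theory of Planned Behavior, exercisers "who have weaker intentions will be flagged and given more attention in terms of support and resources for behavior change".

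For controls, D.13.A describes written information after randomization, weekly calls, voluntary monthly meetings and quarterly newsletters. They also get one call about a personal exercise programme, but only once the intervention has ended.

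**The concern.** The Protocol names comparable attention as a condition for interpreting QOL and says the condition holds. If exercisers have more individual contact, that contact is a second difference between the arms alongside the exercise. Participants know their allocation, and QOL, fatigue, depression and stress are self-reported. QOL is collected at 3 and 6 months, during the contact or just after it. Extra individual support could plausibly raise these scores on its own, in favour of the intervention. A report that repeats the matching statements would then credit exercise itself with a gain that the design cannot separate from support. The concern is weaker for DEXA and serum outcomes, which do not depend on how a woman rates herself.

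**Working it through.** **Figure to check.** The stated figure is equality of contacts over six months, a ratio of 1.0. It involves no sample-size or power calculation.

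**Inputs.** Six months is taken as 26 weeks.

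| Contact | Exercise | Control | Source |
|---|---|---|---|
| Weekly calls | 26 | 26 | D.12.A Telephone Delivery; D.13.A |
| Monthly group activity (voluntary) | 6 events | 6 meetings | D.12.A Voluntary Monthly Events; D.13.A |
| Trainer visits, at least monthly | at least 6 | none described | D.12.A Health-Club Delivery |
| Initial session | 1 | written material only | D.12.A Immediately post-randomization; D.13.A |
| Refresher meetings, extra calls | optional, not counted | none described | D.12.A Cohort Maintenance Program |

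**Plain reading.**

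- Control: 26 + 6 = 32.
- Exercise: 26 + 6 + 6 + 1 = 39 at least.
- Ratio: 39 / 32 = 1.22, so the stated equality is not reproduced.

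**Sensitivity to the reading.**

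- Voluntary group activities left out of both arms: 26 + 6 + 1 = 33 against 26, still 7 more.
- Initial session held by telephone and counted as the first weekly call: 38 against 32, ratio 38 / 32 = 1.19.
- Trainer visit treated as the matched monthly meeting and events not counted: 26 + 6 = 32, or 33 with the initial session, against 32. The ratio is 1.00 to 1.03.

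Only the last reading gives equality or near-equality. The introduction to the intervention in D.12.A does not support it, because it lists monthly in-person booster sessions and monthly physical activity events as separate components. Even on that reading, an individual visit is set against a voluntary group meeting, so the kind of attention still differs.

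**Call minutes.** The exercise call carries the control arm's health topic plus activity review and discussion of barriers. No call length is fixed for either arm, so a difference in minutes can be neither computed nor excluded.

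**What an attention effect would do (illustration only).** The documents give no attention effect on QOL, so a range is assumed. Take the SF-36 SD of 14.88 from Power and Sample Size Considerations, 80 completers per arm (230 × 0.70 = 161, about 80 per arm), an assumed two-sided 0.05 level and no true exercise effect.

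Standard error = 14.88 × √(2/80) = 2.35. The chance of a significant difference is Φ(a/2.35 − 1.96) + Φ(−a/2.35 − 1.96) for an attention effect of a points:

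| a (points) | 0 | 1 | 2 | 3 | 4 | 5 |
|---|---|---|---|---|---|---|
| Probability | 5% | 7% | 14% | 25% | 40% | 57% |

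These figures show sensitivity. They do not estimate the bias.

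**The case against.** Four arguments on the other side deserve weight.

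1. The primary aim compares an exercise intervention with health education, and D.12.A says the trial is an efficacy study that combines components on purpose. Randomization supports a conclusion about that package. This stands. A reader might infer that a QOL gain could not be attributed to exercise at all, but the documents do not support going so far. Weekly calls, a monthly group activity and newsletters are provided in both arms, so much of the contact is controlled.

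2. Sharing the health information and adding exercise training is a deliberate add-on design, openly stated. Coaching and gym access are partly how exercise is delivered. This also stands. The fault lies in the matching statements, not in the add-on.

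3. The trainer visit may be the matched monthly meeting. Procedures to Enhance Adherence speaks of monthly health club meetings and of group support at monthly meetings and events, which gives this some footing. It remains hard to square with the separate listing in D.12.A, and it leaves the optional extra contact and the added attention for weak intenders without a control counterpart.

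4. A reader might infer that exercise calls run longer because they cover more. The documents do not show this. The retention strategies listed under the power section include weekly telephone discussions tailored to each participant, without limiting them to exercisers, so control calls need not be short.

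The net direction of bias is also not settled by the text. D.13.A encourages controls to follow physical activity guidelines, which would dilute a difference. None of this makes the statements of equal contacts and matched attention accurate.

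**Conclusion.** The concern holds in a limited form. The Protocol claims matched attention and time and an equal number of contacts, and its own description of the exercise arm does not have those properties. On the plain reading the excess is at least 7 scheduled contacts per woman (39 against 32, about 22%), before optional contacts. This assumes 26 weeks, six monthly visits and the booster sessions being distinct from the monthly events.

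A QOL difference can be attributed to the exercise programme as a whole. It cannot be attributed to exercise separately from the additional individual contact. How much of a difference that contact might produce cannot be determined from the documents, and no claim about call minutes is justified.

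**What to change.** Reconcile D.13.A, and the comparability sentence under Telephone Delivery, with the rest of D.12.A. Either describe the control-arm counterpart to the initial session and the trainer visits, or remove the statements that attention and time are matched and that contacts are equal in number. Setting a common call length would not be enough, because it leaves the visits and the initial session unmatched.

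In both arms, log the number and minutes of every call, visit and extra contact, and report them by arm beside the QOL result. Unless the logs show equality, state the QOL conclusion as the effect of the whole exercise programme, including its additional contact.

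The cost is one extra field in the contact log, some rewording and a more modest QOL claim. The exercise intervention itself need not change.
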